#### Economic analysis

The economic evaluation takes a broad public sector perspective, including the cost of all health and social services, criminal justice sector costs, and productivity losses as a result of time off work due to illness. The high intensity intervention will be costed on the basis of contact data from records and the salary of the liaison practitioners delivering it, including employer costs (National Insurance and superannuation contributions) and overheads (capital, administrative and managerial) [15]. Other unit costs will be taken from published sources [15-19]. Productivity losses, for young people who are working, will be calculated using the human capital approach, which involves multiplying time off work due to illness by the participant’s salary [20]. Analyses of total cost will compare mean costs using standard *t*-tests to enable inferences to be made about the arithmetic mean [21], and the validity of the results will be confirmed using bias-corrected, non-parametric bootstrapping [22].

Short-run cost-effectiveness will be assessed in terms of incremental cost per true positive and detected using the net benefit approach [23]. The incremental cost-effectiveness ratio (ICER) will be based on parameter estimates from bivariate random effects (‘multilevel’) models, which model costs and outcomes simultaneously, taking account of the hierarchical structure of the data in cluster randomized trials [24,25]. The parameters from the bivariate model will be used to construct cost-effectiveness acceptability curves (CEACs), a recommended decision-making approach, which describes uncertainty around the estimates of expected costs and effects. CEACs are presented by plotting the probability of the intervention being cost-effective for a range of possible values of willingness to pay for a unit improvement in outcome [26]. Since the short-term cost-effectiveness analysis focuses on identification of young people at risk, and not the outcomes for these individuals, decision analytic modeling will be used to explore the relative cost-effectiveness of the interventions in the longer-term [27]. Decision modeling allows assessment of the mean expected costs and outcomes for each arm of the study by modeling a hypothetical cohort of young people identified as at risk. The model will be populated using data on sensitivity and specificity from the cRCT, and data on longer-term care pathways, probabilities, costs and outcomes from a systematic review of the literature. Should gaps remain, expert opinion will be sought [28].

We will select the most suitable modeling framework in which to carry out the analysis, dependent upon the results of the cRCT and the availability of suitable data from the literature. In cases where individuals can be regarded as independent and interaction between them is not an issue in terms of the course or progression of an illness, as is the case in the current population, either a decision tree or a Markov model may be appropriate [29]. Model parameters will be entered into the model with associated probability distributions to explore uncertainty using Monte Carlo simulation, and probabilistic sensitivity analysis will be used to explore the robustness of the model and the impact of alternative model assumptions [27].

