#### Secondary outcomes

New trial-initiated referrals will be assessed by the study team and stratified into individuals who meet criteria for UHR for psychosis or FEP according to the Comprehensive Assessment of At-Risk Mental States (CAARMS) questionnaire (true positives) [10], and people who do not fulfill the criteria (false positives).

We will also perform an economic evaluation that will comprise two components:

1.) Evaluation of the short-run cost-effectiveness of both educational strategies in terms of incremental cost per true positive detected.

2.) Evaluation of longer-term cost-effectiveness using decision analytic techniques.

Data on resource use for costing purposes will be recorded using the Adult Service Use Schedule (AD-SUS) modified for early intervention (EI-ADSUS). The EI-ADSUS was designed on the basis of previous economic evidence in relevant mental health populations [11,12] and was adapted for early intervention following consultation with the clinical team and evidence from the literature [13].

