#### Statistical analysis

In the pre-modeling phase of our analysis, basic descriptive statistics for the total number of referrals, including proportion of true and false positives, will be provided. Subsequent analyses will be carried out separately for true and false positives.

Given that the outcomes are count data, our primary statistical method for modeling will be Poisson regression. If the assumptions of Poisson regression are not met (for example overdispersion), we will use zero-inflated or negative binomial regression models. The fit of the model to the data will be evaluated by comparison of model log-likelihoods. The results will be adjusted for surgery size, considering the number of GPs working in each site as a covariate in the model.

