#### Newsletter

Results from the pilot study [50] revealed that intentions to identify individuals at UHR for psychosis were most strongly predicted by subjective norms. This implies GPs’ perceptions of whether other GPs identify individuals at risk, and whether colleagues or the healthcare system approve, or disapprove, of UHR for psychosis identification, are prominent motivational factors. Therefore, a regular newsletter reporting the participation rates and referral rates for the whole trial area was chosen as a strategy to target this potential causal mechanism to prompt behavioral change.

The thrice yearly newsletter will include graphs to present: 1) the number of referrals that met the criteria for FEP and UHR for psychosis for each of the geographical areas within the county; and 2) a comparison of the number of referrals from primary care and secondary care. This will demonstrate to GPs that other surgeries may also be referring individuals at UHR for psychosis to the trial, while raising awareness that there may be individuals at UHR for psychosis reaching secondary care services before referral to CAMEO.

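### The long-term decision model is to take sensitivity and specificity from the trial, but only referred people are assessed, so absolute sensitivity is not identified and specificity can only be bounded near 1

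*Protocol article*

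**What the plan says.** The Economic analysis section of the protocol article names the source of two inputs to the long-term decision model: "The model will be populated using data on sensitivity and specificity from the cRCT". Care pathways, probabilities, costs and outcomes are to come from a systematic literature review, followed by the fallback "Should gaps remain, expert opinion will be sought". The same section describes the model as "modeling a hypothetical cohort of young people identified as at risk".

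Who is assessed is set out under Secondary outcomes: "New trial-initiated referrals will be assessed by the study team and stratified into individuals who meet criteria for UHR for psychosis or FEP". The instrument is CAARMS. Referred people who meet its criteria count as true positives; all other referred people count as false positives. The Statistical analysis section works with the same two groups: "basic descriptive statistics for the total number of referrals, including proportion of true and false positives, will be provided", and then models each group separately.

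No section describes CAARMS, or any other systematic case-finding, in registered patients who were not referred. The nearest the article comes is the Newsletter section, which compares primary and secondary care referrals and notes that "there may be individuals at UHR for psychosis reaching secondary care services before referral to CAMEO".

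**The concern.** Here the test is GP referral under each educational strategy, and the reference standard is CAARMS. Sensitivity needs the at-risk people whom GPs did not refer (false negatives). Specificity needs the people not at risk who were not referred (true negatives). The design applies the reference standard to test positives only, so neither of these cells is filled by assessment.

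The description of the modelled cohort adds to the difficulty. If people identified as at risk means people referred, everyone in the cohort is test positive. Sensitivity and specificity then have no role within it, and PPV is the relevant input. If the model is meant to start from the registered population, sensitivity is needed and the missed cases are unobserved. The sentence fits neither structure.

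At stake is the second of the two economic components. A model of early detection depends on how many cases each strategy misses and on what happens to them. An input that looks trial-based but actually rests on an unstated prevalence would make that part of the model look better supported than it is.

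**Working it through.** **1. Which cells are observed.**

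| | CAARMS criteria met | CAARMS criteria not met |
|---|---|---|
| Referred | TP, observed | FP, observed |
| Not referred | FN, not observed | TN, not observed |

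- PPV = TP/(TP + FP): estimable.
- Yield per person-year = TP/PY and FP/PY: estimable by arm.
- Sensitivity = TP/(TP + FN): FN unknown.
- Specificity = TN/(TN + FP): TN not verified.

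**2. Inputs from the Sample size calculation section.** Low intensity referral rate 40 per 100,000 person-years (0.0004 per person-year); high intensity rate 0.00080; 2,000 person-years per cluster over 2 years; coefficient of variation 0.15; two-sided 5% level; 80% power; 31 sites per arm. The high rate is printed as per 100,000 person-years. I read it as per person-year, for the reason in step 3.

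**3. Reproducing the plan's own figure.** The unmatched cluster formula for rates gives

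(1.960 + 0.842)² × [(0.0004 + 0.0008)/2000 + 0.15² × (0.0004² + 0.0008²)] / (0.0008 − 0.0004)² = 30.3,

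which rounds up to 31; with the usual one extra cluster it is 31.3. This agrees with the stated 31. Taken literally, 0.00080 per 100,000 gives about 11 per arm, so the per-person-year reading is the one the plan used. The calculation only fixes the inputs for the illustration; the point does not depend on it.

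**4. Share of people assessed.** 2,000 person-years over 2 years is about 1,000 people per site, so about 31,000 per arm. Expected referrals:

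- Low: 0.0004 × 2,000 × 31 = 24.8, or 24.8/31,000 = 0.08% of people.
- High: 0.0008 × 2,000 × 31 = 49.6, or 49.6/31,000 = 0.16% of people.

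More than 99.8% of the age group would not be assessed in either arm.

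**5. Sensitivity for fixed trial data.** The article gives neither PPV nor prevalence. Assume PPV 50% and a prevalence (people meeting criteria during the 2 years) of 0.2% to 5%. TP is then 12.4 (low) and 24.8 (high), and sensitivity = TP/(prevalence × 31,000).

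| Assumed prevalence | Cases among 31,000 | Sensitivity, low | Sensitivity, high | Ratio |
|---|---|---|---|---|
| 0.2% | 62 | 20% | 40% | 2 |
| 1% | 310 | 4% | 8% | 2 |
| 5% | 1,550 | 0.8% | 1.6% | 2 |

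Within an arm the values span a factor of 5/0.2 = 25, all of it from a quantity the trial does not observe. Another PPV would move every sensitivity but leave the factor of 25 unchanged. The ratio between arms is the same in every row: relative sensitivity is identified if prevalence is equal in the two arms.

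**6. Specificity.** With the list as denominator, specificity = 1 − FP/(31,000 − cases). In the high arm at PPV 50%: 1 − 24.8/30,938 = 0.9992 at 0.2% prevalence, and 1 − 24.8/29,450 = 0.9992 at 5%. Over both arms, assumed PPV of 30% to 70% and the same prevalences, it lies between 0.9988 and 0.9998. It can therefore be bounded, but the bound comes from list size and rarity, not from verified negatives.

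**The case against.** Several parts of the case on the other side stand.

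- A reader might infer that neither quantity can be estimated at all. That is too strong. Specificity can be bounded near 1 as in step 6, and relative sensitivity between arms is estimable under randomisation.
- A reader might infer that people whom GPs do not refer are never seen. The documents do not support that. Table 1 describes feedback on each surgery's referrals by source and outcome, and newsletter updates on true cases in the county; the Newsletter section compares primary and secondary care referrals. Some missed cases do reach the service by other routes. This is at most a partial count of false negatives, and it is not presented as one.
- It is tempting to divide the planning rate of 40 per 100,000 person-years by an assumed true incidence and call the result sensitivity. That rate is given for referrals, and Secondary outcomes says that referrals include false positives, so the result would be too high unless PPV were 100%.
- A reader might infer that the long-run cost-effectiveness answer would be wrong. This does not follow. The modelling framework is left open, gaps may go to expert opinion, parameters will carry probability distributions, and the sentence may be loose wording for the true- and false-positive split. Nothing says that PPV will be relabelled as sensitivity.

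An article may also leave model parameters to a fuller economic plan. But this is not a matter of missing detail: the article states a source for two inputs, and that source cannot deliver one of them and can only bound the other. The expert-opinion fallback follows the literature-based inputs and names no parameter, so it does not withdraw the statement.

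**Conclusion.** The point holds in limited form. By its described design the trial identifies PPV, true- and false-positive yield by arm, and relative sensitivity if prevalence is equal in expectation. It does not identify absolute sensitivity, and it gives specificity only as a bound near 1 that hardly discriminates. In the illustration the same high-arm data fit a sensitivity anywhere from 1.6% to 40%. That range rests on an assumed PPV of 50%, an assumed prevalence of 0.2% to 5%, about 1,000 people per site, and 0.00080 read as per person-year. The non-identification itself rests on none of these figures, only on who is assessed.

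The consequence is confined to the secondary long-term economic model. The primary outcome, the sample size and the short-run incremental cost per true positive are untouched.

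**What to change.** Replace the sentence on sensitivity and specificity in the Economic analysis section with text such as:

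> The model will use, by arm, true-positive and false-positive rates per registered person-year aged 16 to 35, and positive predictive value. The between-arm ratio of true-positive rates will serve as relative sensitivity, assuming equal prevalence in expectation under randomisation, with its uncertainty carried through. Absolute sensitivity will enter only through an external prevalence or incidence input from the literature review, matched to the time basis of the model and given a probability distribution in the probabilistic sensitivity analysis.

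The section should also say whether the modelled cohort is the registered population or the people referred, since that decides whether absolute sensitivity is needed at all. If specificity is kept, it should be described as a bound based on list size and a rarity assumption.

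The cost is a change of wording and model structure, plus one external input that the planned review can look for. No new data collection on non-referred patients and no change to trial conduct is required. The downside is reliance on an outside figure and wider uncertainty in the long-term results.

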### Low intensity: the postal information campaign

The main element of the postal information campaign is a specifically designed laminated leaflet (available from the authors), which provides guidelines to help GPs identify and refer individuals at UHR for psychosis. This leaflet will be posted to the surgeries in the low intensity group and integrated within the high intensity educational program (‘high intensity intervention’) to allow investigation of the research question.

Another leaflet had been in routine use for some years in CAMEO, but the trial presented an opportunity to revise it, while not radically changing routine practice in our particular early intervention service that is similar to other services in the region. For the design of the new leaflet, we followed a joint initiative from the MRC and British Psychological Society (BPS), UK, to examine the scientific understanding of the psychological processes involved in the implementation of evidence-based practice guidelines in health services. They recommended the following: 1) guidelines are more closely followed if the wording of behavioral instruction is concrete and precise; 2) the more precisely behaviors are specified, the more likely they are to be carried out; and 3) specifying what, who, when, where and how will assist implementation [30].

In addition, the research team collaborated with a designated advisory group of professionals, including psychologists, psychiatrists, NHS Trust communication teams and GPs. The consensus was that the leaflet should be A4 portrait and on one side only, brief and informative, and with the capacity to be used as a tool for identifying symptoms of individuals at UHR for psychosis. The leaflet was laminated for durability. Amendments and additions were incorporated through several cycles of drafting until a final agreement was reached.

The fundamental requirements were:

1.) An outline of the rationale for early detection of individuals at UHR for psychosis. This included points that were pertinent to GPs (for example halves the risk of suicide), as it has been shown that the more relevant or important the information is to the reader, the more likely they will spend time processing the information [31-34].

2.) A brief description of how individuals at UHR for psychosis might present and who to refer.

3.) Examples of questions for GPs to ask potential individuals at UHR for psychosis to help elicit vital information about underlying sub-threshold psychotic symptoms. This was designed to address Lester *et al*.’s (2005) important finding that GPs had concerns regarding how to phrase sensitive questions about hallucinations, thought disorder and suicide [35].

4.) A list of criteria that would indicate a referral. These were based upon the symptoms included in the CAARMS [10]. Items were presented in a tick-box format because it is well-documented that passive presenting of information is less effective than prompting individuals to engage with the material [36]. Additionally, the use of an algorithmic format has contributed to successful guideline use [37]. Special attention was paid to ensure that the criteria achieved a balance between sensitivity and specificity.

5.) Prominent contact details to facilitate referrals.

### Design of the high intensity intervention

The MRC framework (2008) for the development and evaluation of a complex intervention was used to guide the development of the educational intervention [9]. We also referred to a review providing guidance on the essential components of an effective educational intervention in primary mental health care [32]. This recommended that learning components of the intervention should demonstrate a clinical need and facilitate practical application of new knowledge using examples and data from personal clinical practice. This is essential if clinicians are to recognize their potential needs for improvement. Also, interventions should be multifaceted and supported by practice-based contacts for a period of follow-up.

In conjunction with the factors outlined, we addressed the absence of an explicit, theoretical framework in the design of many educational interventions to change professional practice [38]. We considered the purpose of the intervention to be a change in behavior on the part of professionals.

#### Theoretical framework

There is growing evidence to support the application of psychological models of behavioral change to the clinical behavior of healthcare professionals [39,40]. It helps identify mediators of clinical decision-making [41], and thus allows appreciation of the causal mechanisms responsible for any observed behavior change and valid conclusions concerning the efficacy of the intervention [42].

The theory of planned behaviour (TPB) [43,44] was selected to underpin this research. The TPB is increasingly used to predict intentions and behavior in relation to clinical practice [45]. Ramsey *et al*. (2010) concluded that the TPB was an appropriate theory to predict healthcare professional behavior change and that it offered insight into the processes underlying change in educational interventions in primary care [46]. More pertinent to mental health issues, Green *et al*. (2008) found TPB predictors explained 86% of the variance in GPs’ intentions to refer patients to specialist eating disorder services [47].

The TPB would propose that the act of identifying individuals at UHR for psychosis in primary care is predicted by the strength of a GP’s intention to identify these individuals. This intention is influenced by three predictor variables: 1) whether the GP is in favor of identification (attitude); 2) the intensity of social pressure the GP perceives (subjective norm); and 3) how much the GP feels in control of this identification (perceived behavioral control (PBC)). The measurement of these predictors, pre- and post-intervention, and analysis of their relationship with our objective outcome measure (number of referrals), will enable evaluation of the effect of the intervention on actual behavior and the underlying behavioral process that drive it.

#### Feasibility of theory of planned behaviour (TPB) in primary care

Use of the TBP to design interventions requires the development of a questionnaire to allow the identification and measurement of specific beliefs associated with each construct (intention, attitude, subjective norm and PBC). These beliefs can then be targeted with strategies designed to influence these constructs in the appropriate direction. Strengthening practitioner intentions can be expected to change practitioner behavior in identifying individuals at risk.

In accordance with the TPB guidelines [48,49], pilot work was undertaken away from the study area to identify accessible behavioral, normative and control beliefs. This confirmed the feasibility, reliability and acceptability of administering a TPB-based questionnaire within a representative sample of GPs, to identify beliefs and intentions concerning the identification of individuals at UHR for psychosis. This development and the resulting questionnaire used in this trial are described in detail, elsewhere [50].

#### What TPB predictor variables will be targeted?

A crucial factor in the decision-making process of TPB variables to target was the experimental design of the trial. Strong internal validity is necessary to determine whether the intervention program affects the main outcome measure. If discrete cluster questionnaire scores for the TBP variables are taken into account and predictor variables are targeted accordingly, surgeries in the high intensity group would receive differing interventions. It would then be impossible to make comparisons with the low intensity clusters, draw conclusions about the efficacy of the intervention and identify the potential causal mechanisms for any observed change. Furthermore, research has confirmed that simultaneous maximization of all three TPB variables generated the largest increase in intentions [51]. Therefore, it was decided that all three TPB predictor variables would be targeted for each surgery.

